#### *Per-Protocol Analysis and Compliance Adjustment Analysis*

We will also incorporate a per-protocol analysis to assess the impact of adherence on study outcomes, ensuring a robust evaluation of the intervention's effectiveness beyond intention-to-treat (ITT) analysis.

Per-Protocol Analysis Strategy: Participants will be included in the per-protocol cohort if they meet the following compliance criteria:

- $\geq 70\%$  adherence to meal delivery (defined as receiving and consuming at least 42 of the 60 intervention meals).
- Completion of baseline and 60-day assessments and lab parameters.
- The per-protocol population will be analyzed separately to determine if high adherence to the medically tailored meal intervention is associated with improved clinical outcomes compared to the usual care group.
- Results will be compared to the intention-to-treat (ITT) analysis to identify potential differences in effect size due to adherence variability.

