## 1. C. Pilot Feasibility Trial

Prior to trial enrollment, we conducted a 6-month feasibility trial in which we enrolled a total of 20 patients, to test feasibility of home delivery of meals and obtain patient input on acceptability to optimize our larger scale trial. Our IHS study facilities have a catchment area of over a 50-mile radius. Of 20 patients enrolled, patient's locations of residence are shown in the map.

Given the geographic distance between patients, the rurality of locations, and lack of mailboxes or mailing addresses for many patients, we conducted a pilot feasibility study of 20 patients to ensure feasibility of patient delivery and acceptability of the medically and culturally tailored meals. Patients received 2 meals daily (14 meals weekly) for 4 weeks. Meals were prepared, packaged, and delivered in bulk to our central food hub (Gallup Food Pantry). From there, based on patient preference, a 1-week supply of meals was either picked up weekly by the patient or delivered by preferred patient mode of delivery (delivery to minihub, delivery by CHR, peer delivery). Patients also received 1 cooking class to learn how to make recipes from the meal plan, all incorporating locally available ingredients.

We assessed implementation outcomes including feasibility, acceptability, adoption, and fidelity of the intervention. Complete details on the pilot feasibility study protocol and outcomes are available online.[8][9]. Given implementation success as defined, we will proceed with phase II, with study design and outcomes informed by results of our pilot trial.[9]

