## - Phase II: Comparativeness effectiveness trial of Medically and traditionally tailored meals for Heart Failure

We will conduct a comparativeness effectiveness trial to evaluate the impact of providing medically and culturally tailored Indigenous focused meals delivered to heart failure patients. Meals will be prepared, packaged, and delivered once weekly, with delivery mechanism based on community and patient preference. Two meals will be provided daily for 60 days. Along with the meals, patients will also receive recipe cards with each meal, as well as educational information regarding the meals, traditional food items included, and nutritional information, to educate on the health benefits of the food provided, as well some information regarding the traditional foods included and from where they were sourced. Additionally, patients will receive one cooking class conducted by a Diné Registered Dietician ([name]) to learn how to make a few key recipes from the meal plan, all utilizing locally available ingredients.

**Baseline Characteristics:** In addition to the American Heart Association sociodemographic core measures, we will also collect tribal affiliation, language, and in which local chapter/community patients reside.

**Endpoints:** The primary outcome for the trial will be the proportion of patients who have a hospitalization or ER visit for any cause within 90 days post intervention period (all patients will start the study at t=0 as described above). We will not include hospitalizations that occur electively for an elective procedure.

Secondary outcomes will include: heart failure hospitalizations specifically, ER visits for volume overload specifically (ER visits for lower extremity edema, dyspnea, with clinical evaluation consistent with volume overload), change in weight and body mass index at 60 days from baseline, Kansas City

Cardiomyopathy Score (and its components including summary score, physical limitation score, symptom frequency score, quality of life score and social limitation score)[10], and the following lab parameters and biomarkers at baseline and at 60 days: albumin, prealbumin, creatinine, NT-proBNP, HbA1c, Total cholesterol, LDL-C, HDL-C, Triglycerides, CRP, urine albumin:creatinine ratio. Lab work will be permitted to be collected 14 days before 60 days mark and up to 30 days after (from 46 days-90 days post intervention period).

*Additional secondary outcome measures:*

*Diet Quality*

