Comparator: Those randomized to usual care will not receive any home delivery meals but will receive the recipes of healthy recipes that incorporate traditional local foods and educational booklet. They will also receive a gift bag for agreeing to participate in the study and a \$50 gift card upon completion of the study. Given ethical concerns about those not enrolled to receive the food is medicine intervention, after discussion with our community partners, we will provide 2 meals daily (14 meals weekly) for 4 weeks for all patients randomized to the control group after the study period (and outcome assessment) is complete if patients wish to receive meals and no safety concerns are identified.

Blinding of Intervention: Patients will be informed that they are enrolled in a program to receive medically and culturally tailored meals at home, and thus will not be blinded to their randomization status or participation in this trial. Providers will be not blinded to the intervention. Outcomes will be pulled from the EHR from study members, and those performing the analyses will be blinded to randomization status of the patient.

Enrollment Period: To allow time to coordinate the necessary operational and logistical infrastructure for meal delivery based on patient location/community and delivery mechanism, patients will be

consented and enrolled  $t=-45$  to  $t=-1$  days prior to the start of the intervention period ( $t=0$  for all patients). During this time, baseline assessment with surveys and lab work will take place. All patients will then start the study period (and outcome assessment period) at the same  $t=0$ . Any events that take place in the  $-45$  to  $-1$  days prior to the intervention period will not be included as an outcome. Summary of enrollment, intervention, and outcome assessment timeline is shown below.

[figure not shown]

Intervention Duration: The study team will implement the food intervention for 60 days.

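### The per-protocol adherence count of 42 out of 60 meals conflicts with the 120 meals that the Phase II schedule supplies, so the 70% threshold and its meal count cannot both hold

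*Protocol*

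**What the plan says.** The protocol's section on per-protocol analysis and compliance adjustment has two entry criteria for the per-protocol cohort. The first is adherence of at least 70%, "defined as receiving and consuming at least 42 of the 60 intervention meals". The second is "Completion of baseline and 60-day assessments and lab parameters". The stated purpose is to see whether high adherence goes with better clinical outcomes than usual care, and to compare the result with the intention-to-treat analysis.

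The amount of food is fixed elsewhere. The Phase II description says "Two meals will be provided daily for 60 days", and the Intervention Duration paragraph agrees on the length: "The study team will implement the food intervention for 60 days".

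Under Implementation Outcomes, adherence is recorded in meals: the percentage delivered or picked up, and an end-of-programme survey of how many were eaten.

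**The concern.** The denominator in the adherence definition is half the number of meals the intervention arm is scheduled to receive. The percentage and the count are offered as the same rule, but against the protocol's own schedule they pick out different patients.

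At stake is who counts as adherent. If the analyst applies the count, the cohort can include patients who took little more than a third of the food, and the comparison meant to isolate high adherence is diluted. If the analyst applies the percentage, the cut-off doubles. Left open, that choice could be made after adherence and outcome data are in hand, which a pre-specified threshold is meant to prevent.

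**Working it through.** **Inputs**
- Threshold: at least 70%, glossed as 42 of 60 meals (per-protocol section).
- Supply: 2 meals a day for 60 days (Phase II description; the Intervention Duration paragraph confirms 60 days).
- Weekly supply: 7 × 2 = 14 meals.

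**Step 1: reproduce the stated figure.** 42 / 60 = 0.70. The sentence is correct on its own denominator, so the fault is not in the division.

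**Step 2: rebuild the denominator.** 2 meals/day × 60 days = 120 meals.

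**Step 3: apply the rule to 120 meals.**
- 42 / 120 = 35%.
- 0.70 × 120 = 84 meals.
- 42 meals / 2 per day = 21 days, or 42 / 14 = 3 weeks of food.
- Zone of conflict: 42 to 83 meals, that is 42/120 = 35% up to 83/120 = 69.2%. These patients pass the count and fail the percentage.

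**Step 4: look for any regimen that supplies 60 meals.**

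| Possible source | Meals | 42 as a share | 70% of the meals |
|---|---|---|---|
| 60 days at 2 a day | 120 | 35.0% | 84 |
| 8 whole weekly deliveries | 8 × 14 = 112 | 37.5% | 78.4, so 79 |
| 9 whole weekly deliveries | 9 × 14 = 126 | 33.3% | 88.2, so 89 |
| 4-week regimen | 4 × 14 = 56 | 75.0% | 39.2, so 40 |

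The 4-week regimen appears twice, in the pilot ("Patients received 2 meals daily (14 meals weekly) for 4 weeks") and after the study for controls ("we will provide 2 meals daily (14 meals weekly) for 4 weeks for all patients randomized to the control group"). Neither is the Phase II intervention, and 56 is not 60. No schedule in the protocol gives 60 meals. Rounding Phase II to whole weekly deliveries moves the 42-meal share only between 33.3% and 37.5%.

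**Step 5: test the days reading.** The intervention lasts 60 days, and 42 of 60 days is 70%. But the protocol does not define an adherent day. If one meal eaten were enough, 42 days would need as few as 42 × 1 = 42 meals; if both were required, 42 × 2 = 84. The days reading therefore does not settle the threshold unless an adherent day is defined.

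**The case against.** The best counter-argument is that the 70% is the rule and the count only a gloss. Since 60 is the number of intervention days, the likeliest slip is the word meals written for days; the threshold would then be right and only a noun wrong. This is plausible, and it is why one cannot say flatly that the intended threshold is 35%. It does not remove the conflict: the text says meals, the planned data are in meals, and an analyst following the sentence would count 42 of them.

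Three stronger readings are tempting, and the protocol does not support them.

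- A reader might infer that a patient who stops eating the meals on day 21 automatically enters the per-protocol cohort. Three weeks of food meets the meal criterion only; the baseline and 60-day assessments and laboratory tests must also be complete. The follow-up measures (home delivery after a missed pick-up, calls, home visits) also make a clean stop at day 21 a worst case.
- A reader might infer that the faulty cut-off drives the adherence weighting and the imputation. The weighting paragraph contrasts adherent with non-adherent participants but does not cite the 42-meal cut-off. The imputation paragraph does not say whether the binary flag or the underlying meal data would be imputed. Carry-over is possible, not stated.
- A reader might conclude that the per-protocol analysis cannot show an effect of high adherence. The supportable word is dilutes. The extent depends on how many patients fall between 42 and 83 meals, and the protocol gives no figure for that.

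**Conclusion.** The conflict is real and rests on the protocol's own numbers: a threshold labelled 70% is written as a count that equals 35% of the 120 meals scheduled, half of the 84 that 70% requires. This is a stated figure that contradicts the intervention description, not a detail left for the analysis plan.

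The conclusion assumes that the supply is two meals on each of 60 days, as written, and that adherence is measured in meals. It does not assume which of the two statements the sponsor intended.

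The reach is limited. The primary analysis is by intention to treat, and neither it nor the sample size uses this threshold. The effect falls on a supplementary cohort and possibly on compliance-adjusted analyses. It should be fixed, but it does not threaten the main result.

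**What to change.** Before adherence is classified, reconcile the per-protocol section with the Phase II description by stating the unit, the denominator and the matching count. Two wordings would do this:

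- *at least 84 of the 120 scheduled meals*, which keeps the stated 70% and matches how adherence is collected; or
- *at least 42 of the 60 intervention days*, with an adherent day defined and a means of recording it by day.

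Use the one definition wherever adherence is dichotomised, including any weighting or imputation step that relies on it.

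The cost is a one-line amendment. With 84 meals as the cut-off, the cohort can only stay the same size or shrink compared with 42, so the per-protocol estimate may be less precise. Under the days wording, the size depends on the definition chosen, and daily recording may add to data collection.

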### *Compliance Adjustment Analysis:*

To address differential adherence, the following statistical approaches will be applied:

#### 1. Inverse Probability Weighting (IPW):

- Weights will be assigned based on baseline covariates associated with adherence to adjust for differences between adherent and non-adherent participants.

#### 2. Instrumental Variable (IV) Approach:

- If adherence is influenced by external factors (e.g., household food availability), an IV approach will be explored to estimate the causal effect of the intervention under full compliance conditions.

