**PROTOCOL TITLE: MUTTON-HF (Medically Utilized Tailored Traditional food to Optimize Nutrition) in Heart Failure**

**Version Date 4/30/2025**

**Clinicaltrials.gov Registration: NCT06549699**

## **SECTION 1: RESEARCH PLAN**

### **Statement of Purpose:**

The American Indian and Alaska Native population has experienced significant cardiovascular health disparities compared with other racial and ethnic groups in the U.S. [1] Heart failure, in particular, causes significant morbidity and mortality in Navajo Nation. For many Navajo patients, similar to other American Indian populations, food insecurity is a major driver of health disparities. [2][3] In fact, qualitative data from our heart failure patient advisory committee have found that 89% of patients with heart failure believe nutrition insecurity is a major barrier to optimal health. Dietary factors are believed to be an important cause of hospitalizations in patients with heart failure and cardiovascular outcomes. There is increasing evidence that direct dietary support, such as produce prescription or provision of medically tailored meals may improve cardiovascular outcomes and disease-specific quality of life.[4][5] Furthermore, there has been an increased focus in Indigenous communities to reclaim traditional indigenous foods to improve health. However, more evidence of the benefit of traditional Indigenous foods for cardiovascular health is needed.

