**Randomization:** Randomization in this study will occur at the level of the patient in a 1:1 fashion. Randomization will be stratified by sex, age ( $<65$  years,  $\geq 65$  years) and by left ventricular ejection fraction  $<50\%$  versus  $\geq 50\%$ . Patients living in the same household will be randomized to the same treatment assignment to avoid contamination.

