#### **Statistical Considerations**

Sample Size Determination: The primary outcome is the rate of hospitalization or ER visits within 90 days post randomization. Our preliminary data suggests that the hospitalization rate and ER visit for 90 days is approximately 29%, and based on prior data, we hypothesize a reduction to 13% [4]. We will therefore need a sample size of 204 patients to detect a statistically significant difference with 80% power and an alpha error rate of 0.05.

Interim Analysis: Given no safety concerns during our pilot trial, the short duration of the intervention, and low-risk of the intervention, we will not perform interim safety analyses.

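### As written, the supportive compliance analyses can be biased: household food availability is a poor instrument, and in-window events can keep patients out of the per-protocol cohort

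*Protocol*

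**What the plan says.** Under Statistical Analysis, the primary analysis is by intention to treat. The section Per-Protocol Analysis and Compliance Adjustment Analysis then adds supportive analyses:

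- **Per-protocol cohort.** It requires at least 70% meal adherence, spelled out as 42 meals out of 60, and "Completion of baseline and 60-day assessments and lab parameters". The cohort is compared with usual care, and the result is set beside the intention-to-treat result. The text does not say which criteria apply to controls.
- **Inverse probability weighting.** "Weights will be assigned based on baseline covariates associated with adherence".
- **Instrumental variable.** "If adherence is influenced by external factors (e.g., household food availability), an IV approach will be explored". No other candidate is given. Randomised assignment is not named here, although the Randomization paragraph says "Randomization in this study will occur at the level of the patient in a 1:1 fashion".

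Four other statements bear on these analyses. The Statement of Purpose says that "food insecurity is a major driver of health disparities" and describes diet as a likely cause of heart failure admissions. The Statement of Purpose and Enrollment Period start the 90-day outcome clock at t=0, the same day the meals start. The Phase II description gives two meals a day for 60 days. The Comparator paragraph gives usual care no study meals until outcome assessment has ended.

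**The concern.** **Instrument.** A valid instrument shares no causes with the outcome and affects it only through adherence. Household food availability is observed, not allocated. By the protocol's own reasoning about food insecurity and diet, it plausibly changes the risk of admission whether or not study meals are eaten. The instrumental-variable estimate divides any such direct effect by the instrument's effect on adherence, so a small violation becomes a large bias.

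**Per-protocol cohort.** The 60 days that define adherence lie inside the 90-day outcome window. A long admission or a death can reduce meals eaten or prevent the 60-day assessments, and so take a patient out of the cohort. The meal rule can apply only to the meal arm, because controls receive no meals. Weights built from baseline covariates cannot correct selection that arises from events after randomisation.

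At stake is interpretation. The protocol presents these analyses as strengthening the evaluation beyond intention to treat, so a spurious benefit could be read as support for the primary result, or a spurious null as evidence against it.

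**Working it through.** **1. Inputs and the plan's own figure.** Statistical Considerations states "hospitalization rate and ER visit for 90 days is approximately 29"%, "we hypothesize a reduction to 13"%, and a "sample size of 204 patients to detect a statistically significant difference with 80% power and an alpha error rate of 0.05". With a pooled two-sided test at 1:1 and mean risk 0.21:

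n per arm = [1.96·√(2·0.21·0.79) + 0.8416·√(0.29·0.71 + 0.13·0.87)]² / 0.16² = 100.5, rounded up to 101, so 202 in total.

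The stated 204 reproduces within two patients; power at 102 per arm is 80.6%. The planned effect is 29 − 13 = 16 points. The protocol gives no adherence or length-of-stay figures, so every input below other than 29%, 13% and the meal counts is an assumption.

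**2. Instrument.** Let g be the direct effect of food availability on event risk and π its effect on adherence. With no true meal effect the Wald estimate is g/π.

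| g (points) | π = +10 | π = +20 | π = +40 | π = −20 |
|---|---|---|---|---|
| 0 | 0 | 0 | 0 | 0 |
| −2 | −20 | −10 | −5 | +10 |
| −5 | −50 | −25 | −12.5 | +25 |

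The sign depends on whether having food at home raises or lowers consumption of study meals. The documents do not say, and either is plausible.

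**3. Randomised assignment instead.** Complier effect = intention-to-treat difference / between-arm difference in adherence. For −16 points this is −16/0.9 = −17.8, −16/0.8 = −20.0 and −16/0.7 = −22.9 at assumed adherence of 90%, 80% and 70%. It does not require food availability to be unrelated to the outcome.

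**4. How much the meal rule can exclude.** 2 × 60 = 120 meals. 42/60 = 70%, but 42/120 = 35%; 70% of 120 is 84. At full take-up a patient must miss more than (120 − 42)/2 = 39 days to fall below 42 meals, or more than (120 − 84)/2 = 18 days to fall below 84. At constant hazard the risk by day 60 is 1 − 0.71^(60/90) = 20.4%, so 20.4/29, about 70% of 90-day events, fall in the meal period.

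**5. Simulation with no meal effect.** The assumptions are: 29% risk with constant hazard; take-up averaging 80% (Beta(8,2)); each event before day 60 costs an exponentially distributed stay; 60-day completion is 90% without an event. Per-protocol risk in the meal arm, to be compared with 29% in unselected controls:

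| Threshold | Mean stay (days) | Completion equal | 10 points lower after an event | 30 points lower |
|---|---|---|---|---|
| 42 of 120 | 1 | 28.9% | 26.6% | 21.4% |
| 42 of 120 | 10 | 28.6% | 26.3% | 21.1% |
| 84 of 120 | 1 | 28.6% | 26.3% | 21.1% |
| 84 of 120 | 10 | 23.5% | 21.5% | 17.1% |

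The meal rule alone therefore gives at most about 0.4 points at 42 meals and about 0.4 to 5.5 points at 84. Differential completion adds about 2 to 8 points if controls need not complete.

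**6. Closed-form check.** If a share a of event-free patients and b of event patients qualify, per-protocol risk = 0.29b/(0.29b + 0.71a). With a = 0.8:

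- b = 0.8: 29.0%, no bias
- b = 0.7: 0.203/0.771 = 26.3%, bias −2.7 points
- b = 0.6: 0.174/0.742 = 23.5%, bias −5.5 points
- b = 0.5: 0.145/0.713 = 20.3%, bias −8.7 points

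Against 102 unselected controls, the type I error for the last three is 6.7%, 12.8% and 24.9%.

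**The case against.** The instrumental-variable sentence is conditional and exploratory. Food availability appears as an example of something that influences adherence, and the choice of instrument could be left to an analysis plan that is not at hand. That is fair as to commitment. But it is the only factor tied to the method, so the natural reading makes it the instrument.

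A reader might infer that the per-protocol cohort selects on the outcome itself. The documents do not support that. The criteria concern intake and completion, which events may affect. An ER visit or short stay costs few meals, labs may be drawn from day 46 to day 90, home blood draws and telephone surveys are planned, and non-participants are actively followed. Death is not part of the stated primary endpoint.

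A reader might also take the 8.7-point figure as the expected bias. It assumes sharply different qualification by event status and no selection among controls. Usual care has the same 60-day surveys and labs, so if completion is required in both arms, that part largely cancels under no effect. The −50 in the instrument table likewise needs a weak instrument and one particular sign.

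The overlap of adherence and outcome time rests on the t=0 reading. The Endpoints and sample-size paragraphs word the window differently.

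Finally, randomised assignment also carries an exclusion assumption: the meal arm receives a cooking class, and patients below a cut-off still eat some meals. That stands and must be stated with the fix.

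**Conclusion.** The concern holds as a risk of bias in supportive analyses.

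- **Instrument.** If food availability is used, the estimate is biased in a direction that cannot be known beforehand: 10 to 25 points under an assumed 2 to 5 point direct effect and a 20-point adherence effect.
- **Per-protocol.** The principle holds but the size is unknown. It is near zero from the meal rule alone at 42 of 120 meals. It is about 0.4 to 5.5 points at 84 of 120, with assumed mean stays of 1 to 10 days. It is about 2 to 8 points more if completion differs by event status and is not required of controls.

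It would go too far to infer that all compliance work is unsound or that the trial's main inference is in doubt. Nothing here touches the intention-to-treat primary analysis, and the multiple imputation of adherence data is not shown to be biased.

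**What to change.** 1. **Instrument.** Delete household food availability as an instrument and use randomised assignment. Report the complier average causal effect, i.e. the intention-to-treat risk difference divided by the between-arm difference in adherence. Controls receive no study meals before outcome assessment ends, and members of a household share an arm, so non-compliance is essentially one-sided. State the assumptions: assignment acts only through the defined package of meals plus cooking class, and adherence below any cut-off has no effect. Alternatively, replace the cut-off with the proportion of meals consumed.
2. **Per-protocol, for the hospitalization/ER endpoint.** This endpoint comes from records, so drop the 60-day assessment and lab criterion. Measure adherence against meals due while the patient is alive and out of hospital. State which criteria apply to usual care. Label the comparison as non-randomised and not as confirmation of the intention-to-treat result.
3. **Meal count.** Reconcile the 42-of-60 definition with two meals daily for 60 days, since the strength of the selection depends on it.

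The cost is a change of wording and a standard analysis, with no new kind of data. The complier effect will have a wider interval than the per-protocol comparison.
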